### Participant timeline

Figure 2 provides an overview of the feasibility study time schedule. At the allocation time point (t_−2_), recruited care homes will be randomly allocated to an intervention or control arm. At the enrollment time point (t_−1_), residents within the recruited care homes who are interested in taking part in the study will be asked to provide written consent to undergo two tests to determine their eligibility. If eligible, they will then be asked to provide informed written consent to take part in the feasibility study. The care homes allocated to the intervention arm will be asked to implement the oral health intervention based on the NICE guideline NG48 from baseline (t_0_) to the 12-month time point (t_2_), and the care homes allocated to the control arm will be asked to continue with their usual routine practice during the same 12-month period. Assessments (intervention and control group) will be undertaken at baseline (t_0_), 6 months after baseline (t_1_) and 12 months after baseline (t_2_). All assessments will take place at the care homes. More detailed information about the above processes is provided in the relevant sections below.

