## Interventions

### Explanation for the choice of comparators

Participants on the control arm will receive routine practice. The results from a PHE survey [15] and a PSP on the oral health of older adults [16] suggest that this practice is likely to be heterogeneous and include intermittent tooth brushing with toothpaste by the residents, who usually rely on support from the care home staff for their oral hygiene. This has been confirmed by a review of existing literature on oral health practices in care homes [22], as well as preliminary qualitative research findings from a recent project carried out in care homes in North London (unpublished). The process evaluation will enable the research team to gather information about current practice in care homes assigned to the control arm. Furthermore, collecting information on the control group’s willingness to be randomised to the control arm, as well as follow-up and response rates will help inform and plan for a future larger scale definitive trial.

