**Fig. 2 Fig2:**
[figure not shown]
Time schedule of enrolment, interventions, assessments, and visits for participants. t, timepoint; t_−2_, allocation to study group; t_−1_, enrolment of participants; t_0_, baseline assessments; t_1_, 6-month assessments; t_2_, 12-month assessments

As part of the process evaluation aspect of this study, semi-structured interviews with care home staff and residents will be conducted in parallel to the main trial. Similarly, interviews with key stakeholders will also be undertaken in order to develop a cost-consequence model for the project.

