The second stage will be the recruitment of eligible residents in participating care homes. The aim is to recruit approximately 10 residents per home. A minimum of five and a maximum of 20 participants will be recruited at each care home. For larger care homes, the research team will randomly select a sample of potentially eligible participants. A screening process comprising of three steps will determine eligibility. In step one, the care home manager will identify potentially eligible residents from their personal information stored in the care home records. The care home manager will then pass the names of residents who meet the following criteria to the research assistant: aged 65 years or over, live in the care home full time, not receiving end-of-life care or palliative care, have a good working level of oral English and are currently not taking part in another oral health intervention or programme. Potentially eligible residents will then be given a participant information sheet (PIS) by the care home manager for the two further eligibility tests (as these warrant separate consent). Once consent is obtained (at least 48 h later) for the two further eligibility tests, the research assistant will undertake the 6-CIT test (step two). Residents with normal cognitive function (6-CIT score of 0-7) and those with mild cognitive impairment (6-CIT score of 8-9) will be potentially eligible for inclusion in the study.

In step three, the research assistant will confirm whether the residents are dentate or partially dentate, by performing a brief dental check, known as ‘lift-the-lip’ exercise. If eligible, the research assistant will provide a PIS for the feasibility study and after at least 48 h will ask the resident to complete the informed consent form for the feasibility study (see ‘Who will take informed consent?’ section).

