### Assignment of interventions: allocation

#### Sequence generation

Eligible care homes will be randomised (via North Wales Organisation for Randomised Trials in Health Clinical Trials Unit, NWORTH CTU) at site level based on a 1:1 ratio (six interventions and six controls). Research assistants at each site will inform the NWORTH CTU when there are two eligible care homes. Care homes will be randomised in pairs, using a dynamic adaptive randomisation algorithm [33]. Care homes will be stratified by geographical location (North London/Northern Ireland).

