#### Implementation

Since this is a cluster feasibility trial, participants will be allocated to the treatment that has been assigned to the care home. An independent NWORTH member of staff will allocate the care homes and a research assistant will enrol participants on to the study.

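### Homes are allocated before residents are listed, screened and consented by people not blinded to arm, which puts the consent proportion and the between-arm estimates at risk of recruitment bias

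*Protocol article*

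**What the plan says.** The order of events is explicit. Under Participant timeline, the text runs "recruited care homes will be randomly allocated to an intervention or control arm. At the enrollment time point", and at that next time point "residents within the recruited care homes who are interested in taking part in the study will be asked to provide written consent", first for the eligibility tests and then for the study. The legend to Fig. 2 repeats the sequence: "t_−2_, allocation to study group; t_−1_, enrolment of participants". Under Sequence generation, randomisation is triggered by homes alone: "Research assistants at each site will inform the NWORTH CTU when there are two eligible care homes". No resident list or consent is needed first.

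The people who act between allocation and baseline are these:

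- **Manager.** Under Recruitment for feasibility study, "the care home manager will identify potentially eligible residents from their personal information stored in the care home records". The manager also hands out the information sheet for the eligibility tests.
- **Research assistant.** The same section has the research assistant carry out the 6-CIT and the dental check. Under Implementation, "a research assistant will enrol participants on to the study".
- **Consent taker.** The section on who takes informed consent names a research assistant or a dental examiner for the study consent.

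On blinding, the section on who will be blinded says that homes and residents cannot be, and lists the dental examiners and the statistician as blinded. The section on unblinding calls the study open label and names the statistician as the only blinded party. Research assistants appear as blinded in neither.

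**The concern.** In a cluster trial, concealing the home's allocation protects the choice of home. It does not protect the choice of residents if they are chosen afterwards by people who may know the arm. A manager who knows that staff will be asked to assist with twice-daily brushing may list different residents from one who knows that nothing will change. A resident offered help with mouth care may answer differently from one offered examinations and questionnaires only.

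Two sets of outputs are exposed:

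- **Recruitment parameters.** The Objectives include the proportion of eligible residents who agree to participate. If agreement depends on the arm, a pooled rate mixes two different offers and is a poor basis for planning the definitive trial.
- **Between-arm estimates.** The Outcomes section promises estimates of treatment effects for planning, and the Statistical methods section promises 95% confidence intervals for differences by arm. Intention-to-treat analysis keeps residents in their home's arm, but it cannot repair a difference in who was enrolled.

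**Working it through.** **Step 1: sequence and knowledge of arm.**

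| Step | When | Who | Blinded? |
|---|---|---|---|
| Home allocated | t−2 | Independent CTU staff member | Concealment applies here |
| Residents listed, first information sheet given | after t−2 | Manager | No (homes cannot be blinded) |
| Random selection, larger homes only | after t−2 | Research team | Not stated |
| 6-CIT and dental check | t−1 | Research assistant | Not among the blinded roles |
| Study consent | t−1 | Research assistant or dental examiner | Assistant: not listed. Examiner: the two blinding sections disagree |
| Resident's decision | t−1 | Resident | No |

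The article does not say when a home learns its arm, but nothing holds the result back until consent is complete. Staff in intervention homes must also be trained before residents complete baseline, which is a visible sign of allocation. That research assistants know the arm is an inference from their absence from the blinded roles.

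**Step 2: what the safeguards cover.** Age, full-time residence, palliative care, the 6-CIT cut-off and the dental check leave little discretion. Random selection, where it applies, draws from residents already judged potentially eligible. Neither covers the manager's listing (including the judgement on working English), the invitation or the resident's decision.

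**Step 3: the plan's own figure.** The article gives no figure on this point. Its one precision figure, ±7% for 20% attrition in 120 residents, concerns retention. It reproduces as 1.96 × √(0.20 × 0.80 / 120) = 0.072, treating residents as independent, and does not bear on the matter.

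**Step 4: illustration for the consent proportion (assumed rates).** Suppose 60% of eligible residents agree in intervention homes and 40% in control homes.

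- Eligible residents needed for 60 per arm: 60 / 0.60 = 100 and 60 / 0.40 = 150.
- Pooled rate: 120 / 250 = 48%, which describes neither arm.
- With assumed rates of 70% and 50%, the pooled rate is 58%. With 50% in both arms, it is 50% and nothing is lost.

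Could the study see such a difference? Assume 120 eligible residents per arm, 20 per home.

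- Ignoring clustering, the 95% half-width at 60% and 40% is 1.96 × √((0.24 + 0.24) / 120) = 0.124.
- With an assumed ICC of 0.05, the design effect is 1 + 19 × 0.05 = 1.95, and the half-width is 0.124 × √1.95 = 0.173.

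Differences in consent of moderate size could therefore go undetected.

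**Step 5: scale for the between-arm estimates (assumed ICC).** With 60 per arm and 20% attrition, 48 are analysed per arm, or 8 per home. The standard error of a standardised difference is √(2 × DE / 48), with DE = 1 + 7 × ICC.

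| ICC | DE | SE (SD units) |
|---|---|---|
| 0.01 | 1.07 | 0.211 |
| 0.05 | 1.35 | 0.237 |
| 0.10 | 1.70 | 0.266 |

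A selection shift between arms would have to be read against these values. The document gives no basis for the shift. Purely as an example, at ICC 0.05 a shift of 0.1 SD is 0.1 / 0.237 = 0.4 standard errors and one of 0.3 SD is 0.3 / 0.237 = 1.3.

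**The case against.** The strongest reply is that this is a feasibility study. It has no primary outcome, and its analysis is confined to summaries and confidence intervals. Eligibility rests largely on fixed criteria, larger homes are sampled at random, and most outcomes are also measured at baseline, so a marked imbalance could be seen. The size of any bias is assumed throughout.

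Much of this stands. It limits the exposed area to listing, invitation and consent, and it argues against treating the point as fatal. It does not remove it, because the proportion agreeing to take part is itself an output of a feasibility study.

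Three stronger readings are tempting, and the document does not support them:

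- A reader might infer that the aim of learning about "willingness to be randomised to the control arm" cannot be met, because residents are approached once the arm is fixed. The article attributes this willingness to the control group. Homes agree to take part before they are randomised, so at home level it can be observed.
- A reader might infer that a home recruiting fewer than five residents is lost after randomisation. Five is given as a recruitment minimum. No rule drops a home that misses it, and the analysis is by intention to treat.
- A reader might conclude that baseline should also precede allocation. That conflicts with the Intervention description, where staff in intervention homes are trained before baseline and give the OHAT immediately before the initial dental assessment.

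**Conclusion.** The point holds as a risk built into a stated sequence. Residents are identified, screened and consented after their home's allocation, by an unblinded manager and by research assistants not among the blinded roles. The resident consent proportion and the between-arm estimates and intervals are exposed to identification and recruitment bias. Random selection and fixed criteria reduce the risk without removing it.

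The document does not allow the size to be computed, and it does not show that bias will occur. The 48% pooled rate, the 12 to 17 point half-widths and the standard errors of 0.21 to 0.27 SD rest on assumed consent rates, numbers eligible and ICCs. They show only that a moderate distortion could matter and could pass unnoticed. This should be fixed. It does not invalidate the study.

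**What to change.** Change the trigger for randomisation. Within each pair of recruited homes, complete and lock the manager's list, make any random selection, and finish the 6-CIT, the dental check and the trial consent. The CTU releases the pair's allocation only then. Staff training, the staff-administered OHAT and the baseline assessment follow allocation, so the Intervention description is unaffected. Report eligibility and consent by home and arm.

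If the present order is kept, report approach, eligibility and consent rates separately by arm and not only pooled, and state that the resident consent rate describes consent to a known arm.

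In either case, reconcile the two blinding sections on dental examiners, since examiners may take consent.

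The cost is mainly text: the timeline, both figures, the randomisation trigger and the information sheet. Homes are already randomised in pairs, and the Trial status section says recruitment is postponed, so the change can be made before anyone is enrolled. The sample size of 120 is unchanged. The downside is that each pair waits for its slower home, through two consent stages of at least 48 hours each and the COVID visit conditions. A few consented residents may be lost before baseline.

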**Fig. 2 Fig2:**
[figure not shown]
Time schedule of enrolment, interventions, assessments, and visits for participants. t, timepoint; t_−2_, allocation to study group; t_−1_, enrolment of participants; t_0_, baseline assessments; t_1_, 6-month assessments; t_2_, 12-month assessments

As part of the process evaluation aspect of this study, semi-structured interviews with care home staff and residents will be conducted in parallel to the main trial. Similarly, interviews with key stakeholders will also be undertaken in order to develop a cost-consequence model for the project.

### Sample size

The feasibility study will be conducted in approximately 12 care homes (six interventions and six controls) equally divided between the two settings (North London and Northern Ireland). The aim is to recruit 10 residents per home (a minimum of five and a maximum of 20), resulting in an estimated recruited sample of 120 residents. This sample will allow us to establish the feasibility, rates of recruitment and retention and any delivery issues with the proposed intervention and the research methods. Based on NIHR guidance [32], a sample of 120 participants will allow for an estimated attrition rate of 20% to within a 95% confidence interval of +/− 7%.

The semi-structured interviews with care home staff and residents, and other key stakeholders (process evaluation and cost-consequence model, respectively) will be undertaken until saturation of content is reached.

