#### Concealment mechanism

Randomisation will be at care home level. Once care homes have been entered into the system an independent NWORTH member of staff will allocate the homes using a dynamic adaptive randomisation algorithm [33].

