## Statistical methods

### Statistical methods for primary and secondary outcomes

As this is a feasibility study, statistical analysis will be restricted to generating summary statistics and confidence intervals. The sensitivity and distribution of the outcome measures proposed for the definitive study will be explored. Recruitment and retention outcomes with associated estimates of precision will be summarised. Acceptability of the interventions and outcome measures, clinical indices (including episodes of pain and hospital admissions) and subjective outcomes by study arm will also be summarised and 95% confidence intervals calculated for the difference in means or proportions as appropriate. All statistical analysis will be undertaken on an intention to treat basis taking into account the clustering of participants within care homes. All statistical analyses will be undertaken at NWORTH CTU. A full Statistical Analysis Plan will be written and agreed by the trial team prior to the completion of data collection. This will be made available for comment by the independent committees.

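### The ±7% margin for 20% attrition is computed as if 120 residents were independent and makes no allowance for their recruitment in about 12 care homes

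*Protocol article*

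**What the plan says.** The Sample size section plans about 12 homes, six per arm, with an average of 10 residents in each, "resulting in an estimated recruited sample of 120 residents". After some general feasibility aims it gives one numerical property for that number, attributed to NIHR guidance: "a sample of 120 participants will allow for an estimated attrition rate of 20% to within a 95% confidence interval of" plus or minus 7%. It mentions no ICC, design effect or variation in home size.

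The design is clustered throughout. Under Concealment mechanism: "Randomisation will be at care home level". Under Recruitment for feasibility study: "A minimum of five and a maximum of 20 participants will be recruited at each care home".

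The section on statistical methods for primary and secondary outcomes says that recruitment and retention will be summarised with estimates of precision. It then states: "All statistical analysis will be undertaken on an intention to treat basis taking into account the clustering of participants within care homes".

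**The concern.** The margin in the Sample size section has no term for clustering, while the analysis section promises to allow for it in everything, including the precision of retention. The two sections therefore describe different intervals for the same quantity.

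The protocol itself gives reasons to expect loss to be correlated within homes. Whole homes may withdraw (Criteria for discontinuing or modifying allocated interventions). Face-to-face visits depend on a home having been free of COVID-19 for 14 days (COVID-19). Trial status reports homes closed to all visits. Each of these acts on a home as a unit.

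Retention of homes and residents is a listed objective, and the study is meant to supply parameters for a definitive trial. A reader who takes ±7% at face value would expect a tighter retention estimate than the clustered analysis is likely to give.

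**Working it through.** **Inputs from the protocol article.** Residents n = 120; homes k = 12; mean home size m = 10, range 5 to 20; attrition p = 0.20; 95% confidence; stated half-width 7 points (all from Sample size).

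**Assumed input.** The ICC for attrition is not given. The range 0.01 to 0.10 is used for illustration.

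**Step 1: reproduce the printed figure.** Standard error = √(0.2 × 0.8 / 120) = 0.0365. Half-width = 1.96 × 0.0365 = 0.0716, or 7.16 points, which rounds to 7. The Wilson interval, 13.8% to 28.0%, has nearly the same half-width (7.1 points). The printed value is matched with a design effect of exactly 1.

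**Step 2: allow for clustering.** Design effect DE = 1 + (m − 1) × ICC = 1 + 9 × ICC. Effective n = 120 / DE. Half-width = quantile × 0.0365 × √DE, where the quantile is 1.96 (normal) or 2.201 (t on 12 − 1 = 11 degrees of freedom, because the information comes from 12 homes).

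| Assumed ICC | DE | Effective n | Half-width, normal (points) | Half-width, t on 11 df (points) |
|---|---|---|---|---|
| 0.01 | 1.09 | 110 | 7.5 | 8.4 |
| 0.02 | 1.18 | 102 | 7.8 | 8.7 |
| 0.05 | 1.45 | 83 | 8.6 | 9.7 |
| 0.10 | 1.90 | 63 | 9.9 | 11.1 |

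**Step 3: unequal homes.** DE = 1 + ((CV² + 1) × m − 1) × ICC. An illustrative set of 12 sizes between 5 and 20 that sums to 120 has CV 0.47. This gives DE 1.56 at ICC 0.05 and 2.12 at ICC 0.10. With the normal quantile the half-widths are 8.9 and 10.4 points, against 8.6 and 9.9 for equal homes.

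**Step 4: when does 7% survive?** With the normal quantile and equal homes, the half-width stays below 7.5 points, and so still rounds to 7, only if ICC < ((0.075 / 0.0716)² − 1) / 9, which is about 0.011.

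**The case against.** The arithmetic is correct for independent residents; what is missing is an allowance, and its size depends on an ICC that the document does not give. With normal quantiles the loss is about 0.6 points at ICC 0.02 and 1.5 points at ICC 0.05. No hypothesis test or primary outcome depends on the margin, and the only numerical threshold in the Objectives is 75% completion of measures. All of this stands. It limits the weight of the point but does not make the sentence right for a clustered design. Nor does the appeal to NIHR guidance change the formula that yields 7%.

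A reader might infer more than the documents support:

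- **That ±7% certainly cannot be achieved.** With an ICC near zero (up to about 0.011 on the normal basis) the rounded figure holds. What can be said is that the margin ignores clustering.
- **That one average home withdrawing shifts attrition by 10/120 = 8.3 points, more than the whole margin.** At 20% attrition, two of those 10 residents are already counted as lost. The net shift is 8/120 = 6.7 points, which lies inside 7.16.
- **That the margin misleads about each arm.** The Sample size section claims precision only for the whole sample of 120.
- **That the reported retention interval will be too narrow.** The analysis section already commits to "taking into account the clustering of participants within care homes". The defect is in the planning sentence, not in the planned reporting.

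**Conclusion.** The point holds in a limited form. The ±7% is the independent-binomial half-width, and it conflicts with the clustered design and with the protocol's own commitment to analyse it as clustered. It is the only numerical property given in support of 120 residents, so it should be stated on the right basis.

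For an assumed ICC of 0.01 to 0.10 and homes of 10, the margin becomes 7.5 to 9.9 points with a normal quantile, or 8.4 to 11.1 points with t on 11 degrees of freedom. Unequal homes widen it somewhat further. The t basis is the more suitable with 12 homes. The consequence is lower stated precision for retention. It does not affect power, and it does not show that 120 residents are too few for a feasibility study.

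**What to change.** Leave the sample size as it is. Replace the precision sentence in the Sample size section with one that names its assumptions, for example: *120 residents in 12 homes will estimate a 20% attrition rate to within about ±8 to 11 percentage points for an assumed ICC of 0.01 to 0.10 (10 residents per home, t quantile on 11 degrees of freedom); ±7% would apply only if attrition were essentially uncorrelated within homes and a normal quantile were used.*

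If the trial team has its own basis for an ICC range, it should state that range and recompute the margin. It would also help to note that unequal home sizes widen the margin. The analysis section needs no change.

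The cost is one sentence and a less favourable stated precision; no further residents or homes are needed.
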